## Abstract

**Background::**

As a multisystemic neurodegenerative disorder, Parkinson disease (PD) has a broad spectrum of symptoms including motor and nonmotor symptoms (NMS). As shown in studies, NMS can also impact patient's quality of life, and many of them often go untreated. Chinese herbal medicines with multiconstituent may alleviate NMS in PD patients. This research is carried out to assess the efficacy and safety of a Chinese herbal formula for NMS, with its Chinese name acronym of SQJZ.

**Methods/design::**

It will be a multicenter, randomized, double-blind, placebo-controlled trial. Idiopathic PD with a Hoehn and Yahr scale score ≤4, aged 18 to 80 years, will be involved. About 240 patients will be randomly assigned to either SQJZ or placebo in a 2:1 ratio. There is a 2-week run-in period before the randomization, and the follow-up will be 24 weeks, including 12-week treatment period, with visit once every 4 weeks and 12-week washout follow-up. All participants are asked to maintain the regular medication schedule. SQJZ formula will consist of Chinese herbs with effects for insomnia, constipation, anxiety, and so on. The primary outcome will be measured using NMS scale, and secondary outcomes will include unified PD rating scale, PD sleep scale, the Parkinson fatigue scale, the constipation severity instrument, and PD Questionnaire-39. The primary efficacy analysis will be based on the intention-to-treat method, and mixed-model repeated-measures analyses will be used.

**Discussion::**

The findings from this research might provide evidence of the efficacy and safety of SQJZ Chinese herbal formula for treating NMS in PD patients. The results will sustain the broader use of SQJZ formula in PD.

## Background

1

Parkinson disease (PD) is considered a multisystemic neurodegenerative disorder, together with the classic motor disability, and patients complain about a number of nonmotor symptoms (NMS).^[1–4]^ There is increasing recognition that the NMS of PD is extensive—more than 90% PD patients suffer from NMS.^[5,6]^ They have a significant negative relation with patients’ quality of life.^[6,7]^ NMS have underpinned this conceptual change that PD is a mixed motor, nonmotor, and multiorgan disorder rather than a pure movement disorder.^[8,9]^ The new criteria published for clinical and prodromal diagnosis of PD have incorporated a range of NMS. The PRIAMO study revealed that the most common NMS were fatigue (58%), anxiety (56%), leg pain (38%), insomnia (37%), urgency and nocturia (35%), drooling of saliva, and difficulties in maintaining concentration (31%).^[6]^ Several studies began to focus on NMS. A substudy of ADAGIO showed that rasagiline was associated with significantly less progression of fatigue compared with placebo over a 9-month period.^[10]^ The post hoc analysis of the RECOVER study suggested that rotigotine may benefit patients with sleep, pain, mood, and quality of life.^[11–13]^ However, the prospective study concluded that the improvement of multidomain nonmotor symptoms scale (NMSS) in rotigotine treatment was not superior to placebo.^[14]^ In general, both medicinal and nonmedicinal therapies^[15,16]^ are often advised for PD patients with NMS, but robust evidences for underpinning the clinical effects are limited.

Chinese herbal medicines have a long history used in traditional form for NMS in PD patients, but their real effects are uncertain. Some researchers showed that Chinese herbal medicines improved the NMS of constipation, hyperhidrosis, and sleep disorder.^[17–21]^ Some pilot study also showed that Chinese herbal extract could ameliorate gastroparesis and constipation in PD.^[21,22]^ However, there is still a lack of conclusive evidences to evaluate the efficacy and safety of Chinese herbal medicines by now.

We supposed Chinese herbal formula with multiconstituents may alleviate multiple symptoms at the same time. SQJZ formula, a mixture of Chinese herbs, was developed based on practical experiences from traditional Chinese medicine (TCM), which was responding to the leading symptoms of fatigue, insomnia, and constipation. According to the theory of TCM, the declined function of encephala and the increased toxin of phlegm turbidity are the 2 leading causes for the most manifestations of NMS in PD. Three principles of the prescription are reinforcing function of encephala, purging turbidity by dredging intestines, and tranquilizing mind.

The objective of this study is to assess the efficacy and safety of SQJZ versus placebo for NMS in a randomized clinical trial. As known, PD patients may experience NMS years before Parkinsonism onset,^[23–26]^ can SQJZ improving motor symptoms while improving NMS?

## Methods/design

2

### Study design

2.1

This will be a multicenter, randomized, double-blind, placebo-controlled trial. Participants will be recruited from the PD outpatient of 3 hospitals in Beijing—Dongzhimen Hospital, Beijing Hospital, and Peking University Third Hospital. Patients will be recruited through poster and referral of general practitioners in community healthcare setting. There will be a 2-week run-in period before random allocation. Total research duration will be 24 weeks including 12-week washout follow-up. Participants will be followed up every 4 weeks, and the effect and the safety will be assessed at each visit (Fig. 1).

**Figure 1 F1:**
[figure not shown]
Study design flow chart. There is a 2-week run-in period before the randomization, and the follow-up will be 24 weeks, including 12-week treatment period with visit once every 4 weeks, and 12-week washout follow-up. Estimated 240 patients will be randomly assigned to either SQJZ or placebo in a 2:1 ratio.

### Ethics approval and consent to participate

2.2

The protocol has been approved by Ethics Committee of Dongzhimen Hospital affiliated to Beijing University of Chinese Medicine. Trial will be conducted under supervision of the clinical trials center in Dongzhimen Hospital. General management will follow Good Clinical Practice and Standard Operating Procedures. All data will be anonymized while participants must give written informed consent. Patients may leave this study at any time point without any constraint.

### Selection and inclusion criteria

2.3

Inclusion criteria were as follows: (1) diagnosed as idiopathic PD according to Queen Square brain bank clinical diagnostic criteria^[27]^; (2) Hoehn and Yahr scale score ≤4; (3) male or female aged 18 to 80 years; (4) NMSS score ≥40^[28]^; (5) if receiving a stable dose of levodopa, anticholinergics, dopamine receptor agonists, monoamine oxidase B inhibitors, or amantadine, the subject should be maintained on a stable dose during the study period; (6) informed consent obtained.

Exclusion criteria were as follows: (1) receiving anti-PD drugs (eg, levodopa), but not under the guidance of professional doctors, either concurrently or within 28 days before the baseline visit; (2) receiving any of alpha-methyl dopa, metoclopramide, reserpine, sibelium, neuroleptics, monoamine oxidase-A inhibitors, methylphenidate, amphetamine; (3) receiving sedatives, hypnotics, selective serotonin reuptake inhibitors, anxiolytics, or other sleep-modifying medication unless with a stable dose at least 28 days before the baseline visit;(4) visual hallucination happened within 1 year after PD diagnosis; (5) delirium, epilepsy history, drug or alcoholabuse, serious disease history, or other conditions not suitable to be a participant; (6) laboratory abnormality, for example, serum creatinine ≥97 μmol/L, alanine amino transferase ≥40 U/L, aspartate amino transferase ≥40 U/L; (7) poor compliance; (8) participating in other clinical trials.

### Intervention and control

2.4

All participants will take 2-week placebo in run-in period, then receive either treatment group of SQJZ formula or placebo in the next 12 weeks. SQJZ formula (Table 1), supplied by Beijing Tcmages Pharmaceutical Co., Ltd., will be packed in sealed opaque aluminum sachets with the direction outside, and will be administered twice daily orally by dissolving in 100 mL hot water. The placebo is made of SQJZ (5%) and dextrin (95%).^[29]^ It is also packed in sealed opaque aluminum sachets with the direction outside. Preparation process follow good manufacturing practice guideline to ensure all sourced raw materials, and intermediate and finished products strictly comply with standards of Chinese Pharmacopoeia 2010.

**Table 1 T1:**
[figure not shown]
Primary composition of SQJZ formula.

Conventional western medicines will be maintained at a stable dose during the follow-up period. Glycerine enema will be allowed when participants have no defecation for 3 or more days. Other concomitant medication should also be recorded including the name, dose, and the reasons for use. To improve adherence, we will try to provide ongoing support to patients. Meanwhile, research assistants will give a call to remind the participants 1 week before the next visit, and a hotline will be set up to ensure the doctor–patient communication.

### Randomization and masking

2.5

Patients will be assigned a study (patient) number after consenting to the study. Patients who meet all criteria for enrollment will be randomized to double-blind treatment in a 2:1 ratio. Assignment to treatment groups will be determined by a computer-generated random sequence. SQJZ and placebo is numbered in advance and will be dispensed in sequence. The placebo is made of SQJZ (5%) and dextrin (95%) to insure the mimic appearance, smell, and taste.^[29]^ Both researchers and participants will not know the assignment. The information on intervention assignments will be stored in the third consulting center of biomedical statistics.

### Outcome measures and safety

2.6

The primary outcome will be NMSS, a validated tool for rating frequency and severity of NMS in PD.^[30]^ NMSS domains are as follows: cardiovascular, including falls; sleep/fatigue; mood/cognition; perceptual problems/hallucinations; attention/memory; gastrointestinal tract; urinary; sexual function; miscellaneous. NMSS use a 4-point scale to describe severity and frequency, and higher score indicates more severe conditions. The total NMSS score ranges from 0 to 350. Secondary endpoints include Unified Parkinson Disease Rating Scale (UPDRS),^[31]^ Parkinson Disease Questionnaire-39 (PDQ-39),^[32]^ Parkinson Disease Sleep Scale (PDSS),^[33]^ Parkinson Fatigue Scale (PFS-16),^[34]^ and the constipation severity instrument (CSI).^[35]^ The NMSS, UPDRS, PDSS, PFS-16, and CSI will be assessed at baseline, 4 weeks, 8 weeks, 12 weeks, and 24 weeks. Considering that the quality of life will not be changed in a matter of weeks, the PDQ-39 will be documented at baseline, 12 weeks, and 24 weeks.

During the course of the trial, safety will be assessed through laboratory testing and ECG. Laboratory testing will include liver function and renal function which herbal medicines may injure in the past reports. Participants will get safety assessment at baseline, 4 weeks, and 12 weeks. Investigators are responsible for monitoring the safety of patients who have entered this study. The occurrence and nature of pre-existing conditions including clinically significant signs and symptoms of the disease under treatment in the study will be recorded. Any unfavorable and unintended sign (including an abnormal laboratory finding), symptom, or disease after randomization will be reported as an adverse event, whether or not related to the investigational drug. Adverse events’ record will follow the WHO Adverse Reaction Terminology. Severe adverse events will be reported to Ethics Committee and principal investigator, and be assessed to determine whether further diagnostic investigation or treatment is warranted. If a severe adverse event occurs, appropriate treatment and follow-up will be given.

### Data collection

2.7

Before initiation of the project, investigators from different branch center will participate in training to ensure the standard administration of data collection. The assessments of primary and secondary endpoints will be performed by 2 blinded investigators who are not involved in the randomization at the same time, and final scores will come from the average of the 2 investigators. If participant is unable to continue their face-to-face interview for any reason, we will collect as much information as possible and record it through making phone calls. To promote data quality, double data entry will be used.

### Statistical analysis

2.8

The analysis of the primary variable will be based on the full analysis set: all randomized, treated patients who had a baseline and at least 1 postbaseline measurement for the primary variable. Only when the participant is not taking any drugs after randomization can he be ruled out. For missing value caused by dropout, the remaining date will use the last observation to carry forward. For missing value in the middle of complete cases, the most recent value of not missing date will be carried forward. Analyses of the safety data will be based on the safety set: all patients who were receiving at least 1 dose of trial medication.

Baseline demographic and clinical characteristics will be tabulated as means and standard deviations for continuous variables, and proportions and percentages for categorical variables. Standard baseline characteristics of sex, age, and medical history will be summarized for all patients. Group comparisons will be made using Fisher exact test for categorical data and analysis of variance, with independent factors for treatment of continuous data.

The primary objective of this study is to test the hypothesis that Chinese herbal formula SQJZ will benefit PD patients in alleviating NMS. Mixed-model repeated-measures analyses will be used to assess between-group differences in the modeled change in scores from baseline to 24 weeks. The change score from baseline at each visit will be the dependent variable. Independent variables in the model for fixed effects will be treatment (2 levels: SQJZ and placebo), visit (5 levels: baseline, week 4, week 8, week 12, and week 24), treatment-by-visit interaction, concomitant treatment (yes or no), baseline measures (UPDRS, NMSS), sex, age, and so on. An unstructured covariance matrix will be used to model the within-patient variance–covariance errors. If the unstructured covariance structure matrix results in a lack of convergence, the heterogeneous Toeplitz covariance structure followed by the heterogeneous autoregressive covariance structure will be used. The Kenward–Roger approximation will be used to estimate the denominator degrees of freedom. Similar methods will be used for assessment of secondary endpoints.

For safety analysis, the incidence of adverse events (symptoms, signs, diseases, laboratory tests, or abnormal electrocardiogram manifestations) will be tabulated. Chi-square test or Fisher exact test will be conducted for assessing the differences between SQJZ formula and placebo. All analyses will be performed using the software of Statistics Analysis System by a statistician, blinded to treatment allocation. The data of the trial will be reviewed every 6 months by an independent Data Safety and Monitoring Committee including a neurologist and a statistician, all of whom will be independent of the study.

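### Carrying the last observation forward before the mixed model discards its missing-at-random validity and puts treatment-period scores at the week-24 washout visit

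*Protocol article*

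**What the plan says.** The protocol article, section 2.8 (Statistical analysis), bases the primary analysis on a full analysis set of "all randomized, treated patients who had a baseline and at least 1 postbaseline measurement for the primary variable". Two filling rules follow at once. For dropout: "For missing value caused by dropout, the remaining date will use the last observation to carry forward". For gaps between attended visits: "For missing value in the middle of complete cases, the most recent value of not missing date will be carried forward".

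The same section then gives the only efficacy model: "Mixed-model repeated-measures analyses will be used to assess between-group differences in the modeled change in scores from baseline to 24 weeks". It adds "An unstructured covariance matrix will be used to model the within-patient variance–covariance errors" and "The Kenward–Roger approximation will be used to estimate the denominator degrees of freedom". The abstract agrees: "The primary efficacy analysis will be based on the intention-to-treat method, and mixed-model repeated-measures analyses will be used". Nothing limits carry-forward to a sensitivity analysis, to summary tables or to other endpoints.

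Three other places bear on the point:

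- Section 2.1 gives 24 weeks in total, the last 12 of them washout.
- Section 2.6 measures the Non-Motor Symptoms Scale (NMSS) at baseline and weeks 4, 8, 12 and 24. The visit factor in section 2.8 has the same levels.
- Section 2.9 sizes the trial on an effect of 0.4 at week 12 and about 15% dropout.

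**The concern.** A likelihood-based MMRM with unstructured covariance uses each patient's observed visits as they stand. If missingness depends only on observed data and the model is adequate, its visit contrasts are valid without imputation. Single imputation before the fit takes that property away. Every patient in the full analysis set has at least one post-baseline score, so after filling from the last visit no later visit is missing, and the model has no missing data left to handle.

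The consequence is sharpest at week 24. Treatment ends at week 12, and no NMSS score is scheduled between weeks 12 and 24. A patient without a week-24 score is therefore given one from the treatment period. If benefit fades during washout, these patients are analysed as though it had lasted. Week 24 is not incidental, because the modelled change is stated to run to that visit. At week 12, an early score stands in for a later one, which shifts the contrast whenever the effect is still developing or the arms lose patients at different rates.

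**Working it through.** **The plan's own figure.** The protocol gives no number for the effect of carry-forward, so there is none to reproduce. It does not give trajectories, correlations or dropout timing either. The sizes below rest on assumptions.

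**Inputs from the protocol (section 2.9).** 240 randomised 2:1, hence 160 and 80; effect 0.4 SD at week 12; 15% dropout.

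**Assumptions.** SD of change 1; correlation 0.6 between visits; negative means improvement. SQJZ effect -0.2, -0.3, -0.4, 0 at weeks 4, 8, 12, 24. Trend common to both arms -0.2, -0.3, -0.4, -0.3. Dropout is completely random, with the same hazard in each of the three intervals after week 4. Only dropout was studied, not intermediate gaps.

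**Step 1: what the filled MMRM estimates.** With no gaps, a separate mean for each arm and visit, and unstructured covariance, the visit contrast equals the difference in arm means of the filled scores (covariate adjustment aside). Its expectation is a weighted average of the effects at the last observed visits.

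**Step 2: equal 15% dropout.** The hazard per interval is 1 - 0.85^(1/3) = 0.0527. The shares last seen at weeks 4, 8 and 12 are 0.0527, 0.0500 and 0.0473; 0.8973 are observed at week 12 and 0.85 at week 24.

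- Week 12: 0.0527 × (-0.2) + 0.0500 × (-0.3) + 0.8973 × (-0.4) = -0.384. True value -0.40.
- Week 24: 0.0527 × (-0.2) + 0.0500 × (-0.3) + 0.0473 × (-0.4) + 0.85 × 0 = -0.044. True value 0.

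**Step 3: simulation.** With 4000 trials per scenario, carry-forward was compared with maximum likelihood on the observed visits.

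| Dropout SQJZ / placebo | Week 12, carry-forward (true -0.40) | Week 12, likelihood | Week 24, carry-forward (true 0) | Week 24, likelihood | Week-24 rejection, carry-forward (nominal 5%) |
|---|---|---|---|---|---|
| 15% / 15% | -0.383 | -0.399 | -0.045 | -0.001 | 5.8% |
| 20% / 5% | -0.362 | -0.399 | -0.058 | 0.000 | 7.3% |
| 10% / 25% | -0.406 | -0.400 | -0.031 | 0.000 | 5.8% |
| 30% / 30% | -0.369 | -0.401 | -0.089 | -0.001 | 10.6% |

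The first row agrees with step 2. Rows two and three show that the week-12 error can go either way.

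**Step 4: no treatment effect at any visit.** With equal 15% dropout the carry-forward contrast was -0.001 at week 12 and 0.000 at week 24, with 4.9% rejection at week 12, although both arms changed over time. With unequal, completely random dropout the week-12 shift was +0.015 (20% / 5%) or -0.014 (10% / 25%). It was -0.036 when dropout in the latter setting also depended on the last score. Week-12 rejection in these unequal settings was 5.0% to 5.4%.

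**Step 5: standard error at week 12, 15% dropout.** Carry-forward reports 0.137, which is the complete-data value √(1/160 + 1/80) = 0.137. The spread of its own estimates was 0.136. The spread of the likelihood estimate was 0.1415, and 0.137/0.1415 = 0.97, so the reported error is about 3% below it. At 30% dropout the comparison is 0.138 against 0.148.

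**The case against.** The strongest reply is that the order of steps is not spelled out: carry-forward might have been meant for tabulation, with the MMRM run on observed data. The text does not say so. It places the filling rules directly after the analysis set for the primary variable and names no other efficacy analysis that they could serve. If that was the intention, the wording still needs the same correction.

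A second reply is that section 2.7 provides for telephone collection when face-to-face visits cannot continue. This may reduce the number of gaps, but it leaves the rule for those that remain. Section 2.1 also speaks of four-weekly follow-up, which could suggest washout visits before week 24. The NMSS schedule in section 2.6 and the model's visit levels contain none.

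The third reply concerns size, and much of it stands. Readers might infer four stronger things that do not hold:

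- That carry-forward biases the contrast whenever scores change over time. It does not: a trend common to both arms cancels when dropout is equal (step 4).
- That it always weakens the week-12 effect. With more dropout on placebo it slightly strengthened it (-0.406).
- That its error bars are too small for what it estimates. They are calibrated for its own estimate (0.137 against 0.136). The fair statement is that filled scores are counted as observed information.
- That the plan lacks a sensitivity analysis for data missing not at random. That may sit in a statistical analysis plan which is not shown, so its absence is no finding.

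**Conclusion.** The point holds in this form: a stated rule, applied on the natural reading before a model that does not need it, removes that model's missing-at-random validity and fills the washout visit with treatment-period scores. The week-24 substitution follows from the visit schedule alone. Whether it causes bias depends on whether the effect has changed by then or the arms differ in dropout. Because the direction follows the pattern, carry-forward cannot be defended as reliably conservative.

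At the planned 15% dropout the shift is about 0.02 SD at week 12 and 0.045 SD at week 24, the latter in favour of SQJZ if its effect has gone by then. The 10.6% week-24 rejection needs 30% dropout, twice the planned rate. All these sizes depend on the assumed trajectories, correlation and dropout. The material does not show that the primary week-12 comparison would be seriously distorted at the planned dropout, so this is a should-fix point.

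**What to change.** In section 2.8, delete both carry-forward rules from the primary analysis and state that the MMRM is fitted to the observed visits of every patient in the full analysis set, without imputation. The same wording should cover the secondary endpoints, which use similar methods. If carry-forward is kept, label it as supportive only. A sensitivity analysis under missing not at random (delta-adjusted, or reference-based to placebo) is an optional addition if the analysis plan does not already contain one.

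The cost is a change of wording, best made before unblinding, and a slightly larger reported standard error: about 0.1415 in place of 0.137 SD at week 12 in the 15% scenario. No additional patients, visits or data are needed.

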### Sample size

2.9

According to a previous study,^[14]^ we assumed the effect size of 0.4 in SQJZ treatment compared to placebo at 12 weeks, then a minimum of 204 patients (136 for SQJZ and 68 for placebo). In consideration of a dropout of about 15%, about 240 patients will be needed to achieve a sufficient statistical power of 85% at a significance level (alpha) of 0.05 in 2-tailed test.

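### The primary comparison is worded as change to week 24, twelve weeks after treatment ends, but the trial is sized for a week-12 effect, and no single primary contrast is named

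*Protocol article*

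**What the plan says.** All references are to the protocol article.

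- **Treatment and follow-up.** After the run-in, patients "then receive either treatment group of SQJZ formula or placebo in the next 12 weeks" (Intervention and control). Study design adds: "Total research duration will be 24 weeks including 12-week washout follow-up". The Figure 1 legend agrees.
- **Primary outcome.** Outcome measures and safety states: "The primary outcome will be NMSS, a validated tool for rating frequency and severity of NMS in PD". It attaches no time point. The scale "will be assessed at baseline, 4 weeks, 8 weeks, 12 weeks, and 24 weeks".
- **Primary analysis.** Directly after the primary objective, Statistical analysis says the mixed model will "assess between-group differences in the modeled change in scores from baseline to 24 weeks". The dependent variable is the change score at each visit, and the fixed effects include "visit (5 levels: baseline, week 4, week 8, week 12, and week 24), treatment-by-visit interaction".
- **Sizing.** Sample size says "we assumed the effect size of 0.4 in SQJZ treatment compared to placebo at 12 weeks". From this it derives 204 evaluable patients (136 and 68), raised to about 240 for 15% dropout, for 85% power at two-tailed 0.05.

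Nowhere does the article call week 12 the primary time point. It also gives no expected effect at week 24 and no reason why the week-12 effect should last through the washout.

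**The concern.** The analysis wording points to 24 weeks and the sizing to 12 weeks, and the two weeks measure different things. Week 12 is the end of treatment, so a difference there is an on-treatment effect. A difference at week 24 is what remains after twelve weeks without the study product. A formula that helps while it is taken could miss a week-24 test only because it had been stopped.

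The model also yields several between-group differences: one at each post-baseline visit, and an average over them. If none is named as primary before the data are unblinded, the time point can be chosen after the results are seen. The stated two-sided 0.05 error rate would then no longer be protected.

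**Working it through.** **1. Three readings of the analysis sentence, each set against the sizing**

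| Reading of the 24-week wording | Quantity tested | Matches the week-12 sizing? |
|---|---|---|
| Contrast at week 24 | Difference 12 weeks after treatment ends | No |
| Average over weeks 4, 8, 12 and 24 | Mix of three on-treatment visits and one off-treatment visit | No |
| Span of the visits modelled | Not fixed; a week-12, week-24 or averaged difference could each be reported | Only if week 12 is chosen, and it is not named |

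The missing-data rule blurs a week-24 contrast further. The last observation is carried forward after dropout, so a patient who leaves during treatment would contribute an on-treatment score at week 24.

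**2. The plan's own figure**

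Inputs from Sample size: effect d = 0.4, two-tailed 0.05, power 85%, allocation 2:1.

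Placebo-group size = (1 + 1/2) × ((z_alpha + z_power)/d)².

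- Two-sided: 1.5 × ((1.960 + 1.036)/0.4)² = 84.2, rounded up to 85. The total is 3 × 85 = 255.
- One-sided: 1.5 × ((1.645 + 1.036)/0.4)² = 67.4, rounded up to 68. The total is 3 × 68 = 204.

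So 204 does not follow from the stated two-tailed inputs; a one-sided calculation gives it. The dropout step is right: 204/0.85 = 240. This shortfall is a separate point. It matters here only because it sets the power available at week 12.

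**3. Power at 136 and 68 evaluable, two-sided 0.05**

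Noncentral t with 202 degrees of freedom and critical value 1.972. Noncentrality = d/√(1/136 + 1/68) = d/0.1485.

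| Effect d | Share of 0.4 | Noncentrality | Power |
|---|---|---|---|
| 0.4 | 100% | 2.69 | 76.4% |
| 0.3 | 75% | 2.02 | 52.0% |
| 0.2 | 50% | 1.35 | 26.8% |
| 0.1 | 25% | 0.67 | 10.3% |

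The first row is the week-12 effect assumed in the plan. It would also be the week-24 power if nothing were lost after stopping. The other rows are assumed shares retained at week 24.

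**4. Size needed if week 24 were primary**

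Two-sided formula from step 2, 85% power:

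- d = 0.3: 1.5 × (2.996/0.3)² = 149.6, rounded up to 150; total 450 evaluable.
- d = 0.2: 1.5 × (2.996/0.2)² = 336.7, rounded up to 337; total 1,011 evaluable.

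No power is given for the visit average. It depends on the effect at each visit and on the correlation between visits, and the article states neither.

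**The case against.** The best defence is that the 24-week phrase only describes the span of data entering the model. The next sentence takes the change at each visit as the dependent variable, and the model has a treatment-by-visit term. It can therefore deliver the week-12 difference the trial was sized for, and the full protocol or analysis plan, which is not shown, may name that contrast.

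Much of this stands. A reader might infer that the article fixes the primary test at week 24; it does not, because that is only one reading. A reader might also infer that the planned analysis cannot give the sized quantity; it can, and what is missing is the label. Nor do the documents show that the effect will fade, so the lower power figures are conditional.

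The defence does not remove the conflict. The article does more than leave a detail to another document: it states a 24-week horizon for the primary comparison and a 12-week horizon for the sizing, and nothing in it reconciles them.

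A second objection is that week 24 may be intended, since the Discussion faults earlier trials for not supporting long-term efficacy. That is a legitimate aim. It would need its own effect assumption and its own power, and the article has neither.

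**Conclusion.** The point holds as a mismatch between the stated analysis and the stated sizing, together with a primary contrast that is not fixed. It should be settled before unblinding, because the choice of time point can decide whether the trial succeeds.

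The size of the problem depends on persistence after washout, which the documents do not give. If the full 0.4 persists, a week-24 test has the same 76% power as week 12. Losing a quarter of the effect brings it to 52%, losing half to 27%, and losing three quarters to 10%. These figures assume 136 and 68 evaluable patients, a two-sided 0.05 test of two means at one visit, and the same standard deviation at both weeks.

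**What to change.** Make Statistical analysis and Sample size agree by naming one primary contrast before unblinding: the SQJZ-minus-placebo difference in NMSS change from baseline at week 12, taken from the treatment-by-visit term of the planned model. This is the quantity the trial was sized for. Give the time point in Outcome measures and safety as well, and report week 24 as a secondary estimate of persistence after washout.

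If the sponsor does intend week 24 as primary, the protocol should say so, state and justify an expected effect at that visit, and restate the power or sample size for it.

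Naming week 12 costs a change of wording in two sections, plus the ethics approval that the article requires for any amendment. NMSS is already collected at both visits, so no new data are needed. The change does not by itself restore the stated 85% power: at 204 evaluable the week-12 contrast has about 76%, and the two-tailed inputs call for 255 evaluable, or 255/0.85 = 300 randomized. That has to be dealt with as its own point.
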